### 10.4.2 Dropouts in the control group

Dropouts in the control group (randomized to the control app) can only be study dropouts, because the control app does not include interventions.

Study dropouts are defined as patients who decline further participation OR are **not** answering the daily headache question at least 3 days per week at least 4 weeks consecutively. For this group missing data will be imputed based on data from the control group using reference-based multiple imputations, assuming missing at random (MAR).

### 10.4.3 Missing Data

Data completeness in the diary will be considered on a weekly basis and data are defined as missing if the daily headache question has not been answered at least 3 days per week during a respective week. Missing data for the diary will be imputed on the week-level. Missing data in questionnaires, will be imputed based on the measurement time point. For missing data imputation a multiple imputation procedure will be used (regression based multiple imputation method stratified by treatment group and type of disease (chronic or episodic migraine) with five imputed datasets.

Imputation model: imputations for continuous data will be generated with the predictive mean matching method (pmm). The following variables will be used as predictors in the imputation process for missing values at later time points: headache days, migraine days, age, gender, education level, duration of migraine disease, quality of life (HIT-6), self-efficacy (HMSE-G-SF), headache attributed burden (HALT-30), and migraine-specific health literacy.

In case the respective information for the classification of the headache days into migraine days, days with tension type headaches and other headaches has not been documented, we will use a conservative approach and assume a migraine day. Therefore, we will replace these missing values with migraine days in both groups, for the intervention phase as well as for the baseline phase.

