- Headache attributed burden such as disability and headache attributed lost time is measured with the 5-item Headache-Attributed Lost Time indices (HALT-30^10, official German translated Version) over the last 30 days after 12 weeks. The HALT-30 was developed as part of "The Global Campaign against Headache" with support from the World Health Organization. The HALT items are fully based on the five MIDAS items with slightly changed wording for more clarity and a shorter retrospective reporting period (30 instead of 90 days). Because of this, the HALT-30 can be viewed as an improvement of the MIDAS and the indices show no changes to the structure and scoring of the well-validated MIDAS.
- Migraine-specific health literacy after 12 weeks (3 items, own development) with the items prophylaxis literacy, disease literacy, trigger literacy on a 4 point Likert-type scale from 1="sehr gut" to 4="sehr schlecht".

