Based on this explanation we used the following assumptions as basis for the sample size estimation: reduction of migraine days in the intervention group 1.69 migraine days, and in the control group 0.42 migraine days. This resulted in a group difference of 1.27 migraine days in week 9-12 between both groups with a pooled standard deviation of 4.20. Applying a 2-sided T-test for independent groups with a power of 80% and an alpha of 5%, a total of 173 participants will be needed per group (346 participants in total for both arms). Because the primary analyses will follow the intention-to-treat (ITT) principle, all randomized patients will be included and missing data will be imputed, additional patients to compensate for dropouts have not be taken into account. The sample size was calculated with the software PASS 2008 (Version 08.0.16, Release 27.01.2011; Hintze, J. (2008), NCSS, LLC, Kaysville, Utah).

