## 10.5 ANALYSIS FOR THE EFFECTIVENESS OF THE APP

### 10.5.1 Primary analysis of the primary outcome

The analysis for the primary endpoint (migraine days week 9-12) will be conducted using an analysis of covariance (ANCOVA) with the treatment group (intervention/control) as fixed factor and baseline migraine days (during 28 days) and type of migraine disease (chronic vs. episodic migraine = stratification variable during randomization) as covariates.

The analyses will be based on the ITT population and handling drop out and missing data are defined in chapter 10.4.

From the ANCOVA model, estimated means and 95% confidence intervals, standard errors and the p-value for the group comparison will be obtained. The significance level is set at 0.05 (two-sided).

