### 10.5.3 Moderators and Subgroup Analyses

Moderators on the primary outcome will be analyzed by using an analysis of variance (ANOVA) including an interaction term of the moderator and treatment condition. This will provide information on the importance of each moderator on the treatment effect (p-values and explained variance). We will use the following baseline variables as moderators:

- Gender (male/female/other)
- Baseline migraine days (low vs. high based on median split)
- Type of migraine disease (chronic/episodic migraine)
- Duration of migraine disease (short vs. long based on median split)

In addition to that, we will display for each subgroup means and confidence intervals. These analyses will be considered explorative.

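### Five imputed datasets with no stated seed leave a borderline confirmatory p-value dependent on the random seed; separate imputation by migraine type may also leave sparse chronic cells, depending on a chronic share the plan does not give

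*Combined protocol and SAP*

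**What the plan says.** SAP 10.4.3 calls for a "regression based multiple imputation method stratified by treatment group and type of disease (chronic or episodic migraine) with five imputed datasets", using predictive mean matching for continuous variables. On the diary it says: "Missing data for the diary will be imputed on the week-level". Ten variables are listed as predictors. They include headache days, migraine days, four demographic or history items, the three questionnaire scores and health literacy, which SAP 6.2 describes as three items. The section does not say whether headache and migraine days enter once, as baseline values, or week by week.

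SAP 10.5.1 ties this to the primary analysis: "The analyses will be based on the ITT population and handling drop out and missing data are defined in chapter 10.4". SAP 9.1 makes that analysis the only confirmatory one. SAP 7 makes no allowance for dropout, on the ground that missing values will be imputed.

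Study dropouts are handled by reference-based multiple imputation in SAP 10.4.1 (app arm, copy increments in reference) and 10.4.2 (control arm, control data under missing at random). Neither section states a number of imputations. The SAP gives no seed, no limit on Monte Carlo error, no pooling rule and no fallback for small cells. SAP 11 lists four packages without saying which one imputes.

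**The concern.** A multiply imputed estimate carries simulation noise that shrinks only as the number of imputations, m, grows. With m = 5 the estimate moves from seed to seed, and its between-imputation variance is itself estimated from five values. The trial has one decisive p-value, and the plan relies on imputation for every lost outcome. If the result is near 0.05, two analysts who both follow the SAP could report opposite conclusions, and nothing in the text would settle which is the trial's result.

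A second issue is conditional. Imputing separately in four arm-by-type cells means each chronic-migraine cell must support the whole predictor list alone. If few chronic patients enrol, predictive mean matching there has few donors or cannot be fitted, and the analyst would have to change the model without a rule.

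**Working it through.** **Inputs from the documents.** Difference 1.27 migraine days, SD 4.20, 173 per group, two-sided alpha 0.05, power 80% (SAP 7); m = 5 and the cell structure (SAP 10.4.3).

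**Assumed, because the documents give no figure.** FMI of 5%, 10%, 20% and 30%; a range of chronic-migraine shares; Rubin's rules with small-sample degrees of freedom; five imputations applied to the whole primary analysis.

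**Step 1: the plan's sample size.** The exact two-sided t-test has power 0.7985 at 172 per group and 0.8008 at 173, so 173 is reproduced. The complete-data standard error is 4.20 × √(2/173) = 0.45 days.

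**Step 2: Monte Carlo error.** The estimate from m imputations varies around its infinite-m value with variance B/m, where B = FMI × total variance. The Monte Carlo error is therefore √(FMI/m) standard errors. At m = 5 this is √(0.05/5) = 0.10, √(0.10/5) = 0.14, √(0.20/5) = 0.20 and √(0.30/5) = 0.24. On the day scale at FMI 20%, the standard error becomes 0.45/√0.8 = 0.50, so the Monte Carlo error is 0.20 × 0.50 = 0.10 days. At m = 100 it is √(0.20/100) × 0.50 = 0.02 days.

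**Step 3: effect on the p-value.** For each setting, 200,000 sets of m imputations were simulated, with the estimate drawn as above and the between-imputation variance drawn as B × χ²(m−1)/(m−1). For a trial whose infinite-m p-value is 0.03:

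| FMI (assumed) | p > 0.05, m = 5 | 95% range of p, m = 5 | p > 0.05, m = 50 | p > 0.05, m = 100 |
|---|---|---|---|---|
| 5% | 4% | 0.018–0.054 | 0% | 0% |
| 10% | 15% | 0.014–0.072 | 0% | 0% |
| 20% | 30% | 0.009–0.113 | 0.6% | 0% |
| 30% | 39% | 0.006–0.153 | 3% | 0.3% |

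**Step 4: average over all trials at the design effect.** The true difference is set to 1.27, and two seeds are applied to the same data:

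| FMI (assumed) | Seeds disagree, m = 5 | m = 50 | m = 100 | Power, m = 5 | Power, m = 100 |
|---|---|---|---|---|---|
| 5% | 3.7% | 1.1% | 0.8% | 77.6% | 78.1% |
| 10% | 6.1% | 1.7% | 1.2% | 74.3% | 75.6% |
| 20% | 11.1% | 3.0% | 2.0% | 67.5% | 70.6% |
| 30% | 16.3% | 4.2% | 3.0% | 59.2% | 64.7% |

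Most of the fall below 80% power comes from the lost information. The gap between the last two columns is the part due to m = 5. Type I error at m = 5 stays between 0.048 and 0.051 over these settings.

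**Step 5: chronic cells.** Patients per chronic cell = 173 × chronic share: about 9 at 5%, 17 at 10%, 26 at 15%, 35 at 20% and 52 at 30%. The predictor count is 10 as named, or 12 with three separate literacy items. If both weekly counts from all 11 earlier weeks also enter when week 12 is imputed, 22 are added, giving 32 to 34. Predictors equal patients at these shares:

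- 10/173 = 5.8% and 12/173 = 6.9% with the named list;
- 32/173 = 18.5% and 34/173 = 19.7% with all earlier weeks.

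If 20% of outcomes are missing, 173 × 0.8 = 138.4 observed donors per arm remain. The break-even shares become 7.2% and 8.7%, or 23.1% and 24.6%.

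**The case against.** The strongest reply is that the size is unknown. The plan takes several steps to keep data complete: poor diary users are excluded at baseline, documentation is paid, the app sends reminders, patients who stop the intervention are encouraged to keep recording, and a week counts as missing only if fewer than three days are answered. If FMI is 5% or less, the effect of m = 5 is modest. This stands, and it is why a range is given. The 30% figure also belongs to one borderline case, an infinite-m p-value of 0.03. The averaged disagreement is smaller, and m = 100 does not reduce it to zero.

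A reader might infer that the confirmatory test is invalid or too liberal. The calculation does not support that, since type I error stays near 0.05. A reader might also infer that chronic cells will hold fewer patients than predictors. The documents do not establish this. No chronic share or quota is stated, a 10% share gives about 17 patients against 10 to 12 named predictors, and the count of 32 to 34 requires every earlier weekly value to enter separately, which SAP 10.4.3 does not say.

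Separating the types also has a rationale, because SAP 3 notes that migraine-day levels differ between them. Entering type as a predictor still captures a difference in level. On the other hand, SAP 10.4.1 itself declines to impute from intervention dropouts because that group may be too small, yet no such check is applied to the chronic cells.

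Finally, sections 10.4.1 and 10.4.2 may not be governed by the five in 10.4.3. That is correct, and it leaves the number for study dropouts undefined. The analysis restricted to patients with available values (FAS) needs no imputation of the outcome, but it is exploratory and cannot settle the confirmatory result.

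**Conclusion.** The concern holds for the number of imputations. With m = 5 and no seed, a result near 0.05 is not reproducible from the SAP alone. Over an assumed FMI of 5% to 30%, about 4% to 16% of trials at the design effect would change their significance verdict between two seeds, against about 1% to 3% with m = 100. The power cost of m = 5 relative to m = 100 runs from 0.5 to 5.5 percentage points over the same range. These figures rest on the assumed FMI, on Rubin's rules and on m = 5 applying throughout. The harm is to reproducibility and some power.

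The sparse-cell point is secondary and conditional. Predictors exceed patients per chronic cell only below a chronic share of about 6–7% with the named predictors, or about 18–20% if all earlier weekly values enter. What can be said without an assumption is that the plan gives neither the chronic share, nor the form of the weekly predictors, nor a fallback.

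**What to change.** 1. In SAP 10.4.3, replace five imputed datasets with 100 (at least 50), and pre-specify the seed and the package that will impute. The cost is computing time and one sentence. Going from 5 to 50 captures most of the gain.
2. State in 10.4.1 and 10.4.2 that the same number and a pre-specified seed apply to the reference-based imputations.
3. For the regression-based (predictive mean matching) imputation only, stratify by treatment group and enter migraine type as a predictor, at least when a cell falls below a pre-specified size. Say whether headache and migraine days enter as baseline values or week by week. The price is an assumption that predictor slopes are common to the two migraine types within an arm. This third change does not apply to the control-based reference step.

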### 11 SOFTWARE

SAS for Windows, Version 9.4 (SAS Institute, Cary, NC, USA)

R Version 3.6.2

Stata

SPSS 26.0 (SPSS Inc., Chicago, USA)

Table 2. Secondary outcome analyses for comparisons between both groups

| Outcomes                                                                                    | Time of measurement | Refers to...                                 | Scale       | Possible values | Interpretation                                                 | Analysis method             | Analysis population |
|---------------------------------------------------------------------------------------------|---------------------|----------------------------------------------|-------------|-----------------|----------------------------------------------------------------|-----------------------------|---------------------|
| Migraine days per month                                                                     | daily               | week 1-4, week 5-8                           | continuous  | 0-28            | higher values indicate higher disease burden                   | ANCOVA*                     | ITT                 |
| Headache days per month                                                                     | daily               | week 1-4, week 5-8, and week 9-12            | continuous  | 0-28            | higher values indicate higher disease burden                   | ANCOVA*                     | ITT                 |
| Responder rate: at least 30% reduction of migraine days per month compared to baseline      | daily               | week 9-12                                    | dichotomous | Yes, no         | higher values indicate more responders                         | Binary logistic regression* | ITT                 |
| Moderate/severe headache days per month                                                     | daily               | week 1-4, week 5-8, and week 9-12            | continuous  | 0-28            | higher values indicate higher disease burden                   | ANCOVA*                     | ITT                 |
| Days with acute headache medication intake                                                  | daily               | week 1-4, week 5-8, and week 9-12            | continuous  | 0-28            | higher values indicate higher medication use                   | ANCOVA*                     | ITT                 |

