| Days with triptans intake                                                                   | daily               | week 1-4, week 5-8, and week 9-12            | continuous  | 0-28            | higher values indicate higher medication use                   | ANCOVA*                     | ITT                 |
| Migraine specific quality of life (HIT-6)                                                   | week 12             | week 9-12                                    | continuous  | 36-78           | higher values indicate lower quality of life                   | ANCOVA*                     | ITT                 |
| Self-efficacy (HMSE-G-SF)                                                                   | week 12             | after 12 weeks                               | continuous  | 6-42            | higher values indicate lower impairment                        | ANCOVA*                     | ITT                 |
| Headache attributed burden (HALT-30)                                                        | week 12             | 30 days                                      | continuous  | ≥0              | higher values indicate higher disease burden                   | ANCOVA*                     | ITT                 |
| Migraine-specific health literacy: item prophylaxis literacy                                | week 12             | after 12 weeks                               | continuous  | 1-4             | higher values indicate lower health literacy                   | ANCOVA*                     | ITT                 |
| Migraine-specific health literacy: disease literacy,                                        | week 12             | after 12 weeks                               | continuous  | 1-4             | higher values indicate lower health literacy                   | ANCOVA*                     | ITT                 |
| Migraine-specific health literacy: trigger literacy                                         | week 12             | after 12 weeks                               | continuous  | 1-4             | higher values indicate lower health literacy                   | ANCOVA*                     | ITT                 |

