| Number of patients with concomitant activity/activities against headache (all and specific) | daily               | week 1-4, week 5-8, week 9-12                | dichotomous | Yes, no         |                                                                | Chi             | ITT                 |
| Study dropouts                                                                              |                     | week 1-4, week 5-8, and week 9-12, week 1-12 | dichotomous | Yes, no         |                                                                | Chi             | ITT                 |
| Safety measurements                                                                  |                     |                                              |             |                 |                                                                |                             |                     |
| Counts of serious adverse events                                                            | week 4, 8, and 12   | week 1-4, week 5-8, week 9-12                | continuous  | ≥0              | higher values indicate higher number of serious adverse events | Wilcoxon rank test          | ITT                 |
| Number of patients with at least one serious adverse event                                  | week 4, 8, and 12   | week 1-4, week 5-8, week 9-12                | dichotomous | Yes, no         |                                                                | Chi             | ITT                 |

\* with treatment group (fixed factor) and respective baseline value (if applicable) as covariate

**Table 3.** Descriptive outcomes for the group with M-sense Migräne

| Outcomes                                                        | Time of measurement | Refers to...                  | Scale                                    | Possible values | Interpretation                                                        | Analysis method | Analysis population |
|-----------------------------------------------------------------|---------------------|-------------------------------|------------------------------------------|-----------------|-----------------------------------------------------------------------|-----------------|---------------------|

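### SAP 10.4.3 omits acute-medication, triptan and moderate/severe headache days from the imputation predictors, although Table 2 adjusts each for its own baseline: a minor, easily removed loss in three exploratory outcomes

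*Combined protocol and SAP*

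**What the plan says.** SAP 10.4.3 imputes missing diary data week by week, using regression-based multiple imputation with predictive mean matching, "stratified by treatment group and type of disease (chronic or episodic migraine) with five imputed datasets". It then states "The following variables will be used as predictors in the imputation process for missing values at later time points". The list runs "headache days, migraine days, age, gender, education level, duration of migraine disease, quality of life (HIT-6), self-efficacy (HMSE-G-SF" and closes with "headache attributed burden (HALT-30), and migraine-specific health literacy". Nothing marks the list as a set of examples, and no rule adds each outcome's own earlier values.

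SAP Table 2 includes "Days with acute headache medication intake", "Days with triptans intake" and "Moderate/severe headache days per month". All three are analysed by ANCOVA in the ITT population, and the footnote fixes the model: "with treatment group (fixed factor) and respective baseline value (if applicable) as covariate". A baseline exists for each, because SAP Table 1 marks medication use and moderate/severe headache days in the four-week baseline column.

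Study dropouts are treated separately. SAP 10.4.1 uses copy increments in reference for the intervention arm, and 10.4.2 uses reference-based imputation under missing at random for the control arm. Neither section names its predictors or says whether the 10.4.3 list applies to it.

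**The concern.** An imputation model should contain every variable of the analysis model. If an outcome's own baseline is left out, the imputed values relate to that baseline only as far as the listed predictors stand in for it. The pooled slope is then too flat, and the baseline adjustment removes less variance. If high-baseline participants are missing more often in one arm than in the other, the imputed means are also wrong by different amounts in the two arms, and the difference no longer cancels. At stake are the precision, and in that one situation the accuracy, of the medication, triptan and moderate/severe headache comparisons.

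**Working it through.** **1. List against Table 2.** Migraine days, headache days, HIT-6, HMSE-G-SF, HALT-30 and the health-literacy items all appear both as outcomes and as predictors. The three outcomes above are the only continuous effectiveness outcomes in Table 2 whose own variable is missing from the list.

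**2. The plan's own figure.** The SAP gives no figure for the imputation model. The only figure used here is the sample size: a two-sided t-test with difference 1.27, SD 4.20, alpha 5% and power 80% gives 172.65, rounded up to the stated 173 per group.

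**3. Baseline slope.** Let m be the share of outcomes imputed, ρ the correlation of follow-up with own baseline (equal SDs, so also the slope), and c the correlation of own baseline with the listed predictors taken together. If those predictors inform the follow-up only through the own baseline, imputed values have slope ρc², and the pooled slope is

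slope = ρ[(1 − m) + m·c²].

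With ρ = 0.6 (assumed):
- m = 0.1, c = 0.8: 0.6 × (0.9 + 0.064) = 0.578; simulated 0.574
- m = 0.2, c = 0.6: 0.6 × (0.8 + 0.072) = 0.523; simulated 0.524
- m = 0.3, c = 0.3: 0.6 × (0.7 + 0.027) = 0.436; simulated 0.433

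The simulation used 173 per arm, predictive mean matching by arm, five imputations, Rubin's rules and 500 runs per setting. Assumed were SD 4.2, a true effect of −1.0 day, 10/20/30% missing and c of 0.3/0.6/0.8. It simplifies the plan by not stratifying on migraine type. Over all settings the slope was 0.57 to 0.60 with own baseline and 0.38 to 0.57 without.

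**4. Interval width, whole outcome imputed.** The smallest ratio was 1.557/1.516 = 1.03 and the largest 2.272/1.810 = 1.26, so intervals were 3% to 26% wider.

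**5. How much can be missing.** Under 10.4.1 and 10.4.2, four consecutive weeks below the three-day threshold make a participant a study dropout. A participant who is not a study dropout therefore lacks at most three of the four weeks in any 28-day window. The observed weeks of that outcome are kept.

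**6. Partial against whole missingness.** Assumed: 173 per arm, correlation 0.7 with own baseline, 0.45 and 0.55 with baseline and week-8 migraine days, true effect 1.0 day, and 20-25% of participants affected. For the effect estimates, baseline use was assumed to predict missingness more strongly in controls (log-odds 1.2 against 0.3 per SD).

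| Missing | Effect without own baseline | Effect with it | SE increase |
|---|---|---|---|
| 1-3 weeks | about 0.85 | 1.02 | about 4% |
| Whole 28-day outcome | 0.66 | 0.98 | about 12% |

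The illustrative biases are 1.0 − 0.85 = 0.15 day and 1.0 − 0.66 = 0.34 day. A second run on the same main assumptions gave 0.90 and 0.68, with SE increases of 3-4% and 7%.

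**7. When bias arises.** In the step 3 simulation, bias without own baseline was at most 0.05 day when data were missing completely at random or when missingness depended on baseline equally in both arms. When it depended on baseline in one arm only, bias was 0.14 to 0.52 day without own baseline and 0.02 to 0.06 day with it. The error moved the estimate away from zero there and towards zero in step 6, so its direction is not fixed.

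**The case against.** The strongest reply is that most whole-outcome missingness belongs to study dropouts, who are imputed by other methods. Copy increments in reference and control-arm imputation under missing at random normally start from the participant's own history of the outcome. This largely stands. It confines the certain part of the problem to isolated missing weeks and to intervention dropouts, whom 10.4.1 sends to 10.4.3. It does not close the matter, because 10.4.3 is the only place where predictors are specified.

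The listed variables also act as proxies. Moderate/severe headache days are a subset of headache days and share duration and intensity criteria with migraine. That reduces the loss, but in the simulation it did not remove it even at a correlation of 0.8. Nor can the list easily be read as shorthand for always including the own baseline, since it names the own variable of every other continuous effectiveness outcome.

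A reader might infer that these treatment effects will come out about a third too small. The documents do not support that. It requires the list to govern study dropouts and missingness to depend on baseline use much more in one arm, and the documents give no figure for the latter. A difference between arms is conceivable, since only the full app informs users about medication overuse, but its size is unknown. A reader might also infer damage to the primary analysis; migraine days are in the list, so there is none.

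**Conclusion.** The omission is real and minor. As written, the plan imputes three exploratory ITT outcomes without a covariate of their own analysis model. The reliable consequence is a flatter baseline slope and somewhat wider intervals: about 4% in the partial-missing case, and about 12% only if the list also applies to whole-outcome imputation for dropouts. Wider intervals err on the cautious side. Bias of roughly 0.15 or 0.3 day per true day is conditional on arm-dependent missingness. All these sizes rest on assumed correlations and missing rates, because the documents state neither. The confirmatory result does not depend on this point.

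**What to change.** Add to SAP 10.4.3 that the imputation model for each outcome always contains that outcome's own baseline and its earlier or other observed weekly values, naming acute-medication days, triptan days and moderate/severe headache days. State that the same holds for the reference-based imputation in 10.4.1 and 10.4.2, which also settles how those sections relate to the list. The cost is one or two sentences. All the variables are already recorded in the diary, and no new data or change to the analysis models is needed. Each outcome's own values need only enter its own imputation model, so the models within arm and migraine type grow little.
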